### Interventions

VMMC is the intervention to be evaluated in this study. Men in the intervention group will undergo VMMC within 3 months of randomization, and they could choose one of 2 types of circumcision (disposable circumcision stapler surgery and conventional surgical procedure), while those in the control group will remain uncircumcised during the follow-up. All men will be followed for 12 months.

### Study Outcomes

The primary outcome is HIV incidence, comparing the intervention and control groups. Secondary outcomes are the safety and satisfaction with VMMC; changes in sexual behaviors after VMMC will also be evaluated. The penile HPV incidence, clearance, and persistent infection; HSV-2 incidence; and syphilis incidence are compared in both groups.

### Eligibility Criteria

Individuals who meet all of the following criteria are eligible for enrolment in the CoM Study: (1) aged 18-49 years; (2) assigned male sex at birth; (3) ≥2 male sex partners and ≥10 episodes of anal sex in the past 6 months; (4) practiced insertive role in ≥7 of the last 10 episodes of anal sex with male sex partners; (5) HIV negative; (6) has foreskin that covers over half the glans when the penis is not erectile; (7) is willing to undergo VMMC; (8) resides in the city where a study site is located and has no plan to relocate in the next 12 months; (9) is willing to provide a blood sample and exfoliated penile swabs to test for HIV, HSV-2, syphilis, and HPV; and (10) is able to provide informed consent. Men who are already circumcised or enrolled in other biomedical HIV intervention studies will be excluded. Men who have been diagnosed with a bleeding disorder or have other medical contraindications to VMMC will also be excluded.

### Patient and Public Involvement

There was collaboration with MSM community–based organizations staff who were not involved in the study, to ensure study processes were well integrated into these settings. Patients were not involved in the design of the study.

### Participant Recruitment and Enrollment

As the distribution of our target population unknown and MSM in China are a hard-to-reach population, we will use convenience sampling and snowball sampling to recruit participants. A public account on WeChat (a multi-purpose instant messaging app developed by Tencent, with over 1 billion active monthly users) will be used to communicate with participants. Recruitment, enrollment, provision of health education, and participant follow-up will be accomplished through WeChat. This RCT will also recruit and enroll potential participants in collaboration with local MSM community–based organizations by using their organizational WeChat accounts and in-person outreach activities. An offline survey will be carried out at MSM community–based organizations and the department of dermatology at participating hospitals.

A QR code which links to an online screening questionnaire will be included in recruitment materials. Recruitment materials will include paper materials (eg, posters, folding pages, table tent cards, and business cards) and video materials (ie, a 2-minute enrollment video with a brief introduction and a 15-minute enrollment video with detailed information). Paper and video materials will include summaries of the following: (1) current state of research on efficacy of VMMC to prevent HIV infection; (2) potential benefits of VMMC; and (3) potential risks of VMMC. Potential participants will be invited to scan the QR code included in these paper or video materials and then complete a web-based screening questionnaire with preprogramed logic to assess eligibility.

Eligible men will be invited to participate in this study. Men who agree to participate will receive a face-to-face introduction to the CoM Study by a trained investigator at the study site. Questions about the study will be answered by these investigators during these introductions. For men who are willing to undergo VMMC, HIV rapid testing will be conducted 1 month before enrollment and at enrollment.

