**Methods:**

A multicenter RCT will be conducted among MSM in 8 cities in China. Eligible participants are men aged 18-49 years who self-report ≥2 male sex partners in the past 6 months, predominantly practice insertive anal sex, and are willing to undergo circumcision. Interested men who satisfy inclusion criteria will be tested for HIV 1 month before enrollment and at enrollment, and only those who are HIV negative will be enrolled. At baseline, all enrolled participants will be asked to report sociodemographic characteristics and sexual behaviors; provide a blood sample for HIV, syphilis, and herpes simplex virus type 2 testing; and provide a penile swab for human papillomavirus testing. Participants will be randomly assigned to the intervention or control group. Those in the intervention group will receive VMMC and undergo a web-based weekly follow-up assessment of postsurgery healing for 6 consecutive weeks. All participants will be tested for HIV at 3-, 6-, 9-, and 12-month follow-ups. All participants will also be asked to report sexual behaviors and undergo repeat herpes simplex virus type 2 and human papillomavirus testing at 6- and 12-month follow-ups. The primary end point is HIV seroconversion. Secondary end points are the safety and satisfaction with VMMC and the changes in sexual behaviors after VMMC. The grouped censored data will be analyzed by intention-to-treat approach.

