### Study Measures

The baseline and follow-up surveys will collect information on sociodemographic characteristics (including age, ethnic, educational background, marital status, and monthly individual income) and sexual behaviors (including the number of male and female sex partners, frequency of vaginal or anal sex, condom use, and HIV-positive sex partners) for all enrollment participants. Follow-up surveys will be completed at 6- and 12-month follow-ups. Men randomized to receive VMMC will also be asked to complete weekly follow-up surveys for 6 weeks after VMMC to monitor for postsurgical complications, including pain, poor surgical site wound healing or infection, and premature resumption of sexual behaviors. If an adverse event is reported, trained investigators will contact participants and provide advice on whether further clinical evaluation is needed.

Fingertip blood drop samples will be collected at baseline as well as 3-, 6-, 9- and 12-month follow-ups and tested for HIV using an HIV rapid test. Venous blood samples collected at baseline as well as 6- and 12-month follow-ups will be tested for HIV, syphilis, and HSV-2. Penile swab samples will be collected at baseline as well as 6- and 12-month follow-ups and tested for HPV.

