HIV rapid testing will detect antibodies against HIV-specific antigens using a solid-phase immunochromatographic assay (SD Bioline HIV/Syphilis Duo test; Standard Diagnostics Inc), and these assays will be performed at study sites. Venous blood samples will be tested for HIV using a chemiluminescent microparticle immunoassay (Anti-HIV CLIA Microparticles; Autobio Diagnostics Co) performed at Guangzhou Hybribio Medical Laboratory Limited. If a participant’s sample is found to have a positive result for HIV, we will recollect a venous blood sample from that participant and perform a confirmatory Western blot test at the local Centers for Disease Control and Prevention. Except for HIV, laboratory assays will be applied for syphilis, HSV-2, and HPV test. HPV DNA testing and genotyping was performed using the 37 HPV GenoArray Diagnostic Kit (Hybribio; Chaozhou, China). Syphilis serological tests will be performed using tolulized red unheated serum test and treponema pallidum particle assay. Detection of HSV-2 immunoglobulin G and HSV-2 immunoglobulin M in blood samples are based on a chemiluminescent microparticle immunoassay. Participants who test positive for pathogens or antibodies will be offered STI counseling and referred to a hospital for treatment.

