## Discussion

### Principal Findings

The CoM Study is an RCT to evaluate the efficacy of VMMC to prevent incident HIV infection among MSM in China. MSM who primarily practice insertive anal sex and are willing to undergo VMMC will be recruited using promotional materials disseminated through web-based platforms and community-based organizations. Participants will be randomly assigned to receive or not receive VMMC and then will be followed for a 12-month period to assess incident HIV infection. As an RCT with limited observed person-years, priority will be given to MSM with high-risk sexual behaviors. Follow-up for MSM randomized to receive VMMC will start after a 6-week postsurgical follow-up period to ensure men in the intervention and control groups have comparable opportunity to acquire HIV after enrollment. HIV testing will be conducted every 3 months; it helps to detect acute HIV infection. Findings from this trial will provide preliminary RCT evidence on whether VMMC can effectively prevent HIV among MSM.

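### Antibody-based entry testing lets men infected shortly before enrollment count as incident HIV cases; the size rests on an assumed window, the direction on when intervention men are tested

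*Protocol article*

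**What the plan says.** On entry, the Abstract says that "only those who are HIV negative will be enrolled", and Participant Recruitment and Enrollment says that "HIV rapid testing will be conducted 1 month before enrollment and at enrollment". Study Measures describes the test: "HIV rapid testing will detect antibodies against HIV-specific antigens using a solid-phase immunochromatographic assay".

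A second HIV test is done at baseline: "Venous blood samples collected at baseline as well as 6- and 12-month follow-ups will be tested for HIV, syphilis, and HSV-2". Its assay is given as follows: "Venous blood samples will be tested for HIV using a chemiluminescent microparticle immunoassay (Anti-HIV CLIA Microparticles; Autobio Diagnostics Co". The article names no antigen or nucleic acid test for HIV. Positive results go to a Western blot on a fresh sample.

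On follow-up and outcome: "All participants will be tested for HIV at 3-, 6-, 9-, and 12-month follow-ups", and "The primary end point is HIV seroconversion". Statistical Analysis specifies intention to treat. The Discussion (Principal Findings) adds: "HIV testing will be conducted every 3 months; it helps to detect acute HIV infection".

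On timing, Randomization and Follow-Up has eligible men randomized and then, in the intervention arm, circumcised within up to 3 months of enrollment. Footnote a to Table 2 instead treats intervention men as enrolled only once the circumcision is done.

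**The concern.** A man infected within the antibody window before the enrollment test is negative on that test. He was also negative a month earlier, so the screening test cannot exclude him. He becomes antibody-positive later and meets the end point as worded. The Western blot confirms that he is infected but does not date the infection.

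The primary objective concerns acquisition of HIV. An infection present before randomization cannot be prevented by circumcision. If such cases fall equally in both arms, they dilute the contrast. The design expects only about two events in the circumcision arm, so even one such case is a large share of them.

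**Working it through.** **Inputs from the article (Sample Size).** Incidence is 10 and 2 per 100 person-years, with 120 men per arm, 10% loss and 12 months of follow-up.

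**Reproducing the plan's figure.** Two proportions, 0.10 and 0.02, pooled variance, 80% power:

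n = [z·√(2 × 0.06 × 0.94) + 0.842·√(0.10 × 0.90 + 0.02 × 0.98)]² / 0.08²

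With z = 1.645 this gives 108 per arm, and 108/0.9 = 120, so 240 in total. That z is 1-sided 0.05. At the stated 1-sided 0.10 the same formula gives 79, or 88 after loss (176 in total). This mismatch is a separate matter; here I need only the 108 evaluable men per arm.

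**Assumptions.** The antibody window w is not in the article, so I take 3, 6 and 12 weeks. Incidence before enrollment is taken as 10 per 100 person-years in both arms. The enrollment test is taken to precede randomization, and each arm's year to start at that test. The last is a simplification, because the intervention arm's follow-up clock starts later.

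**Formulas, per arm of 108.**

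- Infections already present at entry: 0.10 × (w/52) × 108.
- Control events: 10.8 + present at entry − 0.10 × (w/52) × 108 = 10.8. The subtraction is for infections still in the window at month 12.
- Circumcision-arm events: 2.16 + present at entry − 0.02 × (w/52) × 108.

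| Assumed window | Present at entry, per arm | Control events | Circumcision-arm events | Ratio (true 0.20) | Apparent efficacy | Share of circumcision-arm events present at entry |
|---|---|---|---|---|---|---|
| 3 weeks | 0.62 | 10.8 | 2.66 | 0.25 | 75% | 23% |
| 6 weeks | 1.25 | 10.8 | 3.16 | 0.29 | 71% | 39% |
| 12 weeks | 2.49 | 10.8 | 4.15 | 0.38 | 62% | 60% |

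Without the month-12 subtraction the ratio is (0.02 + u)/(0.10 + u) with u = 0.10 × w/52, which gives 0.24, 0.28 and 0.35. If the true ratio were 0.44 (the 56% lower odds cited in the Introduction, read as a rate ratio), the first method gives 0.47 to 0.57.

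**Power at 108 per arm (method without the subtraction).**

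| Assumed window | 1-sided 0.10 | 2-sided 0.05 |
|---|---|---|
| none | 88.7% | 69.9% |
| 6 weeks | 84.4% | 62.7% |
| 12 weeks | 80.4% | 56.8% |

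**The other reading of the timing.** Suppose intervention men take the enrollment test after circumcision and their window infections are all screened out, while those in controls stay. At 6 weeks the ratio is then 2.16/(10.8 + 1.25) = 0.18, which overstates efficacy slightly. This is the limiting case.

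**The case against.** Several points against the concern stand.

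- **Other entry test.** The two rapid tests are not the only safeguard, because a laboratory immunoassay is also run at baseline. That it detects only antibody is inferred from its product name. The article says so outright only of the rapid test. So the venous assay is not shown to close the gap, but neither is it shown to be useless.
- **Unseen documents.** A rule for early seroconverters may exist in the full protocol or analysis plan. A reader might infer that the trial has no such rule anywhere; the article cannot show that. What it does fix is antibody-based entry testing with seroconversion as the end point, and followed as written these count infections already present.
- **Direction.** A reader might infer that the effect is certainly pulled toward no effect. That holds only if both arms are tested before randomization. The Abstract, the recruitment section and Randomization and Follow-Up point that way, but footnote a to Table 2 does not.
- **Size.** The window is assumed over a fourfold range, and the 60% share comes only from its upper end. At the stated 1-sided 0.10, power stays above 80% throughout. At 2-sided 0.05 it is already 69.9% with no dilution, so most of that shortfall has another cause.
- **Acute infection.** The Discussion sentence can be read loosely as finding infections sooner through quarterly testing. It defines no end point, so it needs a correction of wording only.

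**Conclusion.** The concern holds in a limited form. Infections present before randomization can enter the primary end point. If the enrollment test precedes randomization in both arms, a true ratio of 0.20 would appear as about 0.25 to 0.29 for assumed windows of 3 to 6 weeks, and 0.38 at 12 weeks. This rests on the article's planning rates, equal incidence before entry and a window that the article does not give. If intervention men are tested after circumcision, the bias could go the other way, to about 0.18 at 6 weeks. The effect is moderate and does not invalidate the trial, but it is worth settling before analysis because few events are expected.

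**What to change.** 1. Reconcile footnote a to Table 2 with Participant Recruitment and Enrollment and with Randomization and Follow-Up. State, for each arm, whether the enrollment HIV test and the baseline venous sample come before randomization.
2. Define the primary end point as HIV infection not present in the pre-randomization sample.
3. For each man whose first positive result is at his first follow-up test, retest the baseline venous sample, where any remains, for HIV RNA or antigen. Do this blind to arm and under the same rule in both arms. Remove those positive from the end point and the at-risk set. The rule uses status before randomization only, so it does not undermine the randomized comparison.
4. Keep the analysis of all seroconversions as a sensitivity analysis.
5. Where no sample remains, do not simply drop first-visit seroconversions. The month-3 test falls about 3 months after enrollment in controls, but up to about 7.5 months after randomization in the intervention arm (3 months' wait + 6 weeks + 3 months), so genuine later infections would be lost unequally. Instead, report a sensitivity analysis that applies the same length of calendar window from the pre-randomization test in both arms, or one over a range of assumed window infections per arm.
6. Correct the Discussion sentence on acute infection.

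The cost is a few laboratory tests, one end-point sentence and the sensitivity analyses, with no added visit. The event count falls slightly. The retest depends on stored baseline samples, and the article does not say whether any are kept.

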### Randomization and Follow-Up

Eligible men will be randomized using a 1:1 allocation ratio to the intervention and control groups. Randomization lists for each study site have been pregenerated by researchers. Each envelope with a unique number will be assigned for 1 allocation sequence, into which a card with grouping information will be put before sealing. Trained investigators at each study site will assign an envelope to each participant according to the order of the participant’s arrival. Participants cannot be blinded due to the nature of the intervention. After randomization, trained researchers will provide HIV prevention counseling to participants in both groups, including promotion of consistent condom use and regular HIV testing.

Participants randomized to the intervention group will be encouraged to complete VMMC within 1 week of enrollment. Time to VMMC can be extended up to 3 months after enrollment on a case-by-case basis. We recommend participants to undergo VMMC at a secondary or higher-level medical center of their own choice. Although the clinical VMMC activities are not part of study procedures, a research assistant would accompany the participants to the hospital to undergo the circumcision. This trial will provide a surgical subsidy of CNY 1000 (US $160). If participants do not complete VMMC within 1 month of enrollment, a text message reminder will be sent. The surgeon will check the condition of the foreskin of participants before the operation to determine if surgery is necessary. Men in the intervention group will be advised to abstain from sex for 6 weeks after undergoing VMMC, and the 12-month follow-up period will begin after this 6-week period of abstinence. If men resume sexual behaviors earlier than 6 weeks after VMMC, then the 12-month follow-up period will begin at the time of their first sexual encounter after VMMC.

Men randomized to the control group will complete the baseline survey after enrollment. The 12-month follow-up period for the control group will begin immediately after completing the baseline survey. At the end of the 12-month follow up period, men in the control group will be offered a CNY 1000 (US $160) subsidy to undergo VMMC.

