**Assessments**							
	HIV rapid testing	**√**	**√**	**√**	**√**	**√**	**√**
	Baseline questionnaire		**√**				
	Follow-up questionnaire				**√**		**√**
	STIs screening^b^		**√**		**√**		**√**

^a^For participants in the intervention group, they will be formally enrolled after completing the circumcision. There is a maximum waiting period of 3 months for surgery and a 6-week postoperative recovery period before formal follow-up phase. For participants in the control group, they will remain uncircumcised at enrollment and follow-up, and they will enter the formal follow-up phase after completing the enrollment and baseline questionnaire.

^b^STIs include herpes simplex virus type 2, syphilis, and penile human papillomavirus.

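### Follow-up starts at different points in the two arms: the pre-surgery wait, which is at-risk time after randomization, is left out of the VMMC arm only, against the stated intention-to-treat analysis

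*Protocol article*

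**What the plan says.** Under Randomization and Follow-Up, the control clock starts at baseline: "The 12-month follow-up period for the control group will begin immediately after completing the baseline survey". For men assigned to VMMC, "the 12-month follow-up period will begin after this 6-week period of abstinence"; if they resume sex sooner, "the 12-month follow-up period will begin at the time of their first sexual encounter after VMMC".

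The target is surgery within 1 week, but "Time to VMMC can be extended up to 3 months after enrollment on a case-by-case basis". The Interventions section counts the same limit from randomization: "Men in the intervention group will undergo VMMC within 3 months of randomization". Table 2, footnote a, adds the two parts of the gap: "There is a maximum waiting period of 3 months for surgery and a 6-week postoperative recovery period before formal follow-up phase". That footnote also says of VMMC men that "they will be formally enrolled after completing the circumcision", whereas Table 2 places group assignment at month 0 and Randomization and Follow-Up counts the wait for surgery from enrollment.

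The Discussion (Principal Findings) explains the delayed start after the 6-week postsurgical period as a way "to ensure men in the intervention and control groups have comparable opportunity to acquire HIV after enrollment". Statistical Analysis states that all data will be analysed by intention to treat, with a Poisson model that assumes a constant baseline hazard.

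**The concern.** In a randomized comparison, both arms are normally observed from the same point, the date of randomization. Here the VMMC clock starts at an event after randomization, and in one branch that event is the man's own sexual behaviour. Two stretches of time fall outside VMMC follow-up with no matching gap for controls: the wait for surgery and the healing weeks.

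The healing weeks have a stated reason. The wait does not. During it the men are uncircumcised and have not been advised to abstain, so they carry the same risk as controls.

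Footnote a adds a further difficulty. If VMMC men are enrolled only once circumcised, a man assigned to VMMC who never has surgery may have no clock at all. This could happen, because the surgeon decides before the operation whether it is needed. Leaving such men out would conflict with intention to treat.

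The design expects very few VMMC infections, so a handful of early ones, handled one way or the other, can change the primary result.

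**Working it through.** **Inputs from the article.** Control incidence 10/100 person-years, VMMC incidence 2/100, 120 men per arm, 10% loss (Sample Size); wait of 1 week (target) to 3 months (maximum); healing period of 6 weeks = 42 days = 1.38 months.

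**Assumed.** The article gives no distribution of waiting times. I take three cases in which every man waits 1 week, 1 month or 3 months.

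**The plan's own figures.**
- Rate ratio: 2/10 = 0.20. Over one year in 120 men per arm, 120 × 0.10 = 12 control and 120 × 0.02 = 2.4 VMMC infections.
- Sample size: at one-sided 0.10 and 80% power, the log rate ratio formula gives (1.2816 + 0.8416)² × (1/0.10 + 1/0.02) / (ln 0.2)² = 104.4 person-years per arm. Dividing by 0.9 gives 116.02, so 117 per arm, close to the stated 120.
- Power: the two-proportion formula with 108 evaluable men per arm (120 × 0.9) gives 88.7% at one-sided 0.10. I use this formula for all power comparisons below.

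**Offset of the VMMC clock.** Wait plus 1.38 months: 1.6 months (1 week), 2.4 (1 month), 4.4 (3 months). Early resumption of sex shortens it.

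**Time to the first follow-up HIV test.** There are two readings:
- Month 0 precedes surgery. No test is listed at the delayed start, and the first follow-up test can fall 4.38 + 3 = 7.4 months after randomization, against 3 months for controls.
- The enrollment test follows surgery, as footnote a suggests. The gap after that test is 1.38 + 3 = 4.4 months, and infections during the wait could be picked up at that test.

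**Infections during the wait.** 120 × wait in years × 0.10. If they are counted but their person-time is not, the rate ratio is (2.4 + wait infections)/12.

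| Wait (all men) | Infections in wait | Rate ratio if counted without person-time |
|---|---|---|
| 1 week | 0.23 | 2.63/12 = 0.22 |
| 1 month | 1.0 | 3.4/12 = 0.28 |
| 3 months | 3.0 | 5.4/12 = 0.45 |

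If they are dropped, the ratio stays at 0.20, but infections in randomized men have been removed from one arm.

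To show how much a few events matter: 12 versus 2 infections in 120 per arm gives a two-sided Fisher p of 0.011, and 12 versus 5 gives 0.13.

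**Both arms from randomization, 12 months.** VMMC rate = w × 0.10 + h × a + (1 − w − h) × 0.02. Here w is the wait in years, h = 42/365.25 = 0.115, and a is the rate during abstinence (assumed 0 to 0.02). For a 1-month wait and a = 0: 0.0083 + 0 + 0.8017 × 0.02 = 0.0244, so the ratio is 0.24.

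| Wait (all men) | Rate ratio | Power, one-sided 0.10, 108 per arm |
|---|---|---|
| As planned | 0.20 | 89% |
| 1 week | 0.19–0.22 | 87–89% |
| 1 month | 0.24–0.27 | 83–85% |
| 3 months | 0.38–0.40 | 67–70% |

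**The case against.** The delayed start is deliberate and partly sound. Counting weeks of advised abstinence would credit VMMC with low-exposure time, and the stated objective is efficacy, so an analysis from the end of healing answers a legitimate question. That argument stands for the 6 weeks. It does not reach the wait.

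The target wait is 1 week and extensions are case by case. If most men meet the target, about 0.23 infections are affected and the ratio moves only to 0.22. The 0.45 needs every man to wait the full 3 months. This also stands, and it limits the size of the point.

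Three stronger readings are tempting, and the documents do not support them:
- A reader might infer that VMMC men certainly go more than 7 months untested and that early infections cannot be told from later ones. This holds only if month 0 precedes surgery; footnote a allows the other reading.
- A reader might infer that early infections are bound to be either dropped or counted without person-time. The article says neither. Counting them with person-time from randomization is not excluded, and such detail is commonly left to a fuller document. What the article does fix is the arm-specific start of follow-up.
- A reader might infer that the shift in time biases the ratio by itself. Under the plan's constant hazard it does not; that would need risk to change over follow-up, for which the documents give no figure.

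Anchoring at randomization also dilutes the estimate, since it counts the wait too. The difference is that it counts infections and person-time together, for the groups as randomized.

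**Conclusion.** The point holds and should be fixed. The article sets a different time zero in each arm, about 1.6 months apart at the target wait and at most about 4.4. It justifies the healing weeks but not the uncircumcised wait, and so departs from the intention-to-treat analysis that it announces. Footnote a and the Randomization and Follow-Up section disagree on whether enrollment comes before or after surgery, which leaves both the HIV test gap and the status of never-circumcised men unclear; these passages must be reconciled.

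The direction of any bias depends on handling: dropping infections from the wait favours VMMC, and counting them without their person-time works against it. The size runs from negligible (ratio 0.22) to large (0.45). It rests on the design incidence of 10/100 person-years before surgery and on assumed waiting times.

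**What to change.** - Define the primary analysis from the date of randomization in both arms, for all randomized men, circumcised or not. Count every confirmed seroconversion after randomization, with person-time from randomization and the actual HIV test dates.
- Keep the analysis from the end of healing as a labelled secondary analysis.
- Reconcile Table 2, footnote a, with Randomization and Follow-Up on when VMMC men are enrolled and when the month-0 HIV test is taken.
- Leave the visit schedule unchanged. Recruitment closed in July 2022, and moving visits would be an operational change. VMMC tests will therefore straddle 12 months from randomization, so the text should say where follow-up is cut.

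The change is to analysis wording and uses randomization and test dates that the trial should already hold. The price is an estimate that includes the wait and, with it, the power loss shown above: slight at a 1-week wait, moderate at 1 month, and a fall from about 89% to 67–70% if every man waited 3 months.
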